## **9.2. PHASE II TRIALS**

### **9.2.1.Primary endpoint**

- Primary objective is to investigate the antitumor activity of Regorafenib when prescribed in association with Avelumab, independently for 17 cohorts of patients : Colorectal cancer not MSI-H or MMR-deficient (cohorts A and A' with immune signature (based on low tumor-associated macrophages infiltrate level), GIST (Cohort B), Oesophageal or gastric carcinoma (cohort C), Biliary tract cancer, hepatocellular carcinoma (Cohort D), Soft Tissue Sarcoma (STS – Cohort E), Radioiodine-Refractory Differentiated Thyroid Cancer (RR-DTC – Cohort F), Neuroendocrine gastroenteropancreatic tumors (GEP-NETs – Cohort G), Non-small cell lung cancer (Cohort H), Solid tumors (including Soft Tissue Sarcoma) with immune signature (TLS+) (Cohort I), urothelial cancer (Cohort J), HPV-associated cancer (Cohort K), triple negative breast cancer (L), TMB-high solid tumors (Cohort M), MSI-high solid tumors (Cohort N), non clear-cell renal carcinoma (Cohort O) and malignant pleural mesothelioma (Cohort P).
- For cohorts A, as well as C to G, antitumor activity will be assessed in terms of objective response under treatment based on adapted RECIST 1.1 criteria, and after in-stream centralized radiological review:

- Objective response under treatment is defined as patients with confirmed complete response (CR) or partial response, as per RECIST v1.1 criteria, observed during treatment with the investigational product(s).
- As per RECIST v1.1 criteria, to be considered as “confirmed”, complete and partial responses will have to be confirmed at least 4 weeks later to ensure responses identified are not the result of measurement errors. If the new imaging to confirm response is not performed after 4 weeks, complete or partial responses will be considered as unconfirmed responses.
- Objective response rate (ORR) under treatment is defined as the proportion of patients with objective response (confirmed or unconfirmed) under treatment based on adapted RECIST 1.1 (taking into account “unconfirmed “responses).
- For cohorts B (GIST), H (NSCLC), I (Solid tumors -TLS+), M (TMB-high solid tumors), N (MSI-high solid tumors), O (non clear-cell renal carcinoma) and P (malignant pleural mesothelioma), antitumor activity will be assessed in terms of 6-month progression-free rate (6-month PFR) based on RECIST 1.1 criteria after in-stream centralized radiological review. 6-month PFR is defined as the proportion of patients with progression-free status at 6 months. Progression-free status is defined as complete response (confirmed or unconfirmed), partial response (confirmed or unconfirmed) or stable disease more than 24 weeks as defined as per RECIST v1.1 criteria.
- For cohort A' with immune signature (based on low tumor-associated macrophages infiltrate level) antitumor activity will be assessed in terms of 4-month progression-free rate (4-month PFR) based on RECIST 1.1 criteria after in-stream centralized radiological review. 4-month PFR is defined as the proportion of patients with progression-free status at 4 months. Progression-free status is defined as complete response (confirmed or unconfirmed), partial response (confirmed or unconfirmed) or stable disease more than 24 weeks as defined as per RECIST v1.1 criteria.
- For cohorts J (Urothelial cancer), K (HPV-associated cancer) and L (Triple negative breast cancer): antitumor activity will be assessed in terms of disease control rate at 6-month (6-month DCR rate) based on RECIST 1.1 criteria after in-stream centralized radiological review. 6-month DCR rate is defined as as the proportion of participants with confirmed complete response (CR), unconfirmed complete response (CRu), confirmed partial response (PR) or unconfirmed partial response (PRu) or stable disease (SD), as per adapted RECIST v1.1, observed within 24 weeks of treatment onset (while treated with the investigational product).

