##### 10.3.2.2. PHASE II TRIALS

- All analyses will be descriptive; no p-values will be calculated.
- Analyses will be conducted independently for each phase II trial.
- Analysis of the primary efficacy endpoint will be analysed based on the eligible population assessable for efficacy (see chapter 10.2 for definition):
  - Each patient will be assigned one of the following categories:
    - Confirmed complete response (CR)
    - Unconfirmed complete response (CRu)
    - Confirmed Partial response (PR)
    - Unconfirmed Partial response (PRu)
    - Stable disease
    - Progression (Clinical PD and radiological PD will be reported separately)

- Inevaluable for response
- Depending on the cohort, the rate of objective response (ORR: CR, CRu, PR, PRu) under treatment or the progression-free rate (PFR: CR, CRu, PR, PRu, SD) will be reported:
  - All eligible and assessable patients (section 10.2) will be included in the denominator for the calculation of the ORR/PFR.
  - The 95% two-sided confidence limits will be provided for the ORR/PFR (binomial law).
  - First endpoint conclusions will be based on the ORR/PFR for all eligible and assessable patients (section 10.2) after centralized radiological review of the data.
- As regards to the other efficacy endpoints, the analyses will be carried out in the eligible and assessable population:
  - Each patient will be assigned one of the following categories:
    - Confirmed complete response (CR)
    - Unconfirmed complete response (CRu)
    - Confirmed Partial response (PR)
    - Unconfirmed Partial response (PRu)
    - Stable disease
    - Progression
    - Inevaluable for response
  - The rate of best overall response will be calculated as the number of patients alive with the best response (recorded from the start of the treatment) divided by the number of patients eligible and assessable (section 10.2).
  - The 6-month progression-free rate will be calculated as the number of patients remaining alive and progression-free at 6 months from the start of the treatment divided by the number of patients eligible and assessable (section 10.2).
  - The 6-month objective response rate will be calculated as the number of patients alive with complete or partial response at 6 months divided by the number of patients eligible and assessable (section 10.2).
  - The 95% two-sided confidence limits will be provided for the calculated rates (binomial law)
- The safety analysis will be performed on the safety population.

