## Definition of the Best Response

The best response determination in trial where confirmation of complete or partial response is required:

Complete or partial responses may be claimed only if the criteria for each are met at a subsequent time point as specified in the protocol (**generally 4 weeks later**). In this circumstance, the best overall response can be interpreted as in Table below.

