**Table 3 – Best overall response when confirmation of CR and PR required.**

| Overall response
First time point | Overall response
Subsequent time point | BEST overall response                                           |
|--------------------------------------|-------------------------------------------|-----------------------------------------------------------------|
| CR                                   | CR                                        | CR                                                              |
| CR                                   | PR                                        | SD, PD or PR a                                       |
| CR                                   | SD                                        | SD provided minimum criteria for SD duration met, otherwise, PD |
| CR                                   | PD                                        | SD provided minimum criteria for SD duration met, otherwise, PD |
| CR                                   | NE                                        | SD provided minimum criteria for SD duration met, otherwise NE  |
| PR                                   | CR                                        | PR                                                              |
| PR                                   | PR                                        | PR                                                              |
| PR                                   | SD                                        | SD                                                              |
| PR                                   | PD                                        | SD provided minimum criteria for SD duration met, otherwise, PD |
| PR                                   | NE                                        | SD provided minimum criteria for SD duration met, otherwise NE  |
| NE                                   | NE                                        | NE                                                              |

CR = complete response, PR = partial response, SD = stable disease, PD = progressive disease, and NE = inevaluable.

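### For cohorts A and C to G, objective response is defined as confirmed CR or PR, but the analysed ORR also counts unconfirmed responses; failed and pending confirmations have no stated class.

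*Protocol*

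**What the plan says.** Section 9.2.1, repeated in the synopsis under the phase II primary endpoint, gives two statements for cohorts A and C to G. The event: "Objective response under treatment is defined as patients with confirmed complete response (CR) or partial response, as per RECIST v1.1 criteria". The rate, two bullets later: "Objective response rate (ORR) under treatment is defined as the proportion of patients with objective response (confirmed or unconfirmed) under treatment". Between them is the rule for a missing repeat scan: "If the new imaging to confirm response is not performed after 4 weeks, complete or partial responses will be considered as unconfirmed responses".

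Section 10.3.2.2 follows the wider version, reporting "the rate of objective response (ORR: CR, CRu, PR, PRu) under treatment".

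Appendix 3, in its part on trials where confirmation is required, says: "Complete or partial responses may be claimed only if the criteria for each are met at a subsequent time point". Its Table 3 classes a PR followed by no evaluable assessment as "SD provided minimum criteria for SD duration met, otherwise NE", and a PR followed by SD as SD. The table has no category for CRu or PRu.

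Section 10.1.2 feeds this ORR into Bayesian stopping rules with a Beta(1,1) prior. The first look comes after 16 weeks of follow-up of the first 10 patients, and further looks follow every 5 patients up to 50. Section 5.5 schedules scans every eight weeks, plus a repeat at least four weeks after a first response.

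On a secondary endpoint, Section 10.3.2.2 also says: "The rate of best overall response will be calculated as the number of patients alive with the best response". Section 9.2.2 defines best response across all time points.

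**The concern.** The ORR is the count that drives every interim recommendation in six cohorts, and the protocol describes its event in two ways. Three kinds of patient are affected.

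- **No repeat scan.** The response is labelled unconfirmed. It is outside the event definition but inside the analysed numerator.
- **Repeat scan done, response not confirmed.** Section 9.2.1 gives no class. Table 3 makes PR then SD a stable disease.
- **Repeat scan not yet due.** A response first seen on the week-16 scan cannot have been confirmed when that patient's 16-week follow-up triggers a look. This arises even with full compliance, and no rule says how the response counts.

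Section 9.2.1 gives measurement error as the reason for confirmation. The wider count admits responses that have not passed that check. Where the count is one response short of a bound, the handling of a single patient settles the recommendation.

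**Working it through.** **Inputs (Section 10.1.2).** Prior Beta(1,1); looks at n = 10, 15, …, 50; stop for inefficacy if the probability that ORR is at or below p0 is at least 80%; stop for efficacy if the probability that ORR is at or above p1 is at least 80%. Thresholds p0/p1 are 5%/20% (A, E), 20%/40% (C, D, F) and 10%/25% (G). The protocol states no response-count bounds or error rates for these cohorts, so there is no figure of its own to reproduce. I read *predictive probability* as posterior probability and treat n = 50 as the last look.

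**Step 1: one response at a bound.** With x responses in n patients the posterior is Beta(1+x, 1+n−x), so P(ORR ≥ p1) = P(Bin(n+1, p1) ≤ x).

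A and E, n = 10, p1 = 0.20:
- x = 2: 0.8^11 + 11(0.2)(0.8^10) + 55(0.2²)(0.8^9) = 0.086 + 0.236 + 0.295 = 0.617, continue.
- x = 3: add 165(0.2³)(0.8^8) = 0.221, giving 0.839 before rounding of the terms, stop for efficacy.

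The same check at n = 10 elsewhere:

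| Cohorts | Rule | One side of the bound | Other side |
|---|---|---|---|
| G | efficacy | 3/10: 0.713, continue | 4/10: 0.885, stop |
| C, D, F | efficacy | 5/10: 0.753, continue | 6/10: 0.901, stop |
| C, D, F | inefficacy | 0/10: 0.914, stop | 1/10: 0.678, continue |

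The bounds are the same whichever numerator is used. For A and E the efficacy bounds are 3/10, 5/15, 6/20, 7/25, 8/30, 9/35, 10/40, 11/45 and 13/50. Only the count set against them changes.

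**Step 2: effect over all looks.** If a share s of counted responses is unconfirmed, counted ORR = confirmed ORR/(1−s). The protocol gives no s, so I show a range. For A and E at a confirmed 5%, s = 10% gives 5.56% and s = 30% gives 7.14%. Exact binomial recursion over the looks, with the confirmed ORR at p0:

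| Cohorts | Efficacy stop, s = 0 | s = 10% to 30% | Inefficacy stop, s = 0 | s = 10% to 30% |
|---|---|---|---|---|
| A, E | 1.2% | 1.6% to 3.1% | 16.6% | 13.5% to 7.5% |
| C, D, F | 1.0% | 1.9% to 8.0% | 36.7% | 26.3% to 9.0% |
| G | 2.0% | 3.0% to 7.7% | 31.2% | 25.1% to 13.2% |

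For A and E, adding 3 to 5 percentage points to a confirmed 5% gives 4.3% to 8.0%. That needs s = 3/8 = 37.5% to 5/10 = 50%.

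**Step 3: the cost in the other direction.** With s = 20% and the counted ORR at p1, a confirmed-only numerator lowers the chance of an efficacy stop:

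| Cohorts | Counted ORR | Confirmed ORR | Efficacy stop, counted | Efficacy stop, confirmed-only |
|---|---|---|---|---|
| A, E | 20% | 16% | 50.6% | 29.3% |
| C, D, F | 40% | 32% | 45.1% | 15.1% |
| G | 25% | 20% | 49.4% | 25.2% |

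**The case against.** The strongest reply is that the primary ORR can be determined. Section 9.2.1 bases the rate on an adapted RECIST 1.1 and says in brackets that unconfirmed responses are taken into account; Section 10.3.2.2 lists CRu and PRu. The phase II PFR, DCR and 6-month ORR also accept unconfirmed responses. On this view one word is loose in the event definition. That largely stands. A reader might infer that the protocol leaves two equally valid ORRs, but the text does indicate which is analysed. What remains is a stated event that disagrees with the analysed numerator.

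Other parts of the reply also stand:

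- **Appendix 3.** Table 3 applies where confirmation is required, so the adapted rule can override it. It is a weaker conflict than the one inside Section 9.2.1.
- **Skipped scans.** A reader might infer that omitting the repeat scan earns a success. The scan is mandatory, and a later eight-weekly scan, centrally read, can itself confirm. Nothing shows how often responses would stay unconfirmed, or that sites would behave this way.
- **Inflation.** Calling a crossing false assumes p0 and p1 refer to the confirmed ORR. Section 10.1.2 says only that the maximal thresholds rest on investigators' opinions. If both refer to the counted ORR, there is no inflation. The rules also only recommend stopping.

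The reply does not cover failed and pending confirmations, which have no stated rule in Section 9.2.1.

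**Conclusion.** The point holds as an inconsistency between the stated event and the analysed numerator, with two cases left unclassed. It deserves correction because the endpoint drives the interim recommendations and one response is enough to change one. That result needs no assumption about the unconfirmed share, only the posterior reading of the 80% rules.

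The size of any inflation is not established. For A and E at a confirmed 5%, it is modest under an assumed share of 10% to 30% (1.2% to at most 3.1%). A reader might infer a rise to 4.3% to 8.0%, but that requires 37.5% to 50% of counted responses to be unconfirmed, which nothing in the protocol supports. Nor do the stopping bounds move.

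The word *alive* in the best-overall-response numerator is a separate, smaller fault. Read literally, it drops a responder who later dies. It has no bearing on the primary ORR or the stopping rules.

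**What to change.** 1. Choose one numerator and state it identically in the synopsis, Section 9.2.1, Section 10.3.2.2 and Appendix 3, and name it as the count entering the stopping rules of Section 10.1.2.
2. Class a response that its repeat scan fails to confirm as a non-response.
3. State how a response awaiting its repeat scan counts at a look.
4. Report the other count, confirmed-only or confirmed plus unconfirmed, as a sensitivity analysis.
5. Separately, delete *alive* from the best-overall-response numerator in Section 10.3.2.2.

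Keeping the wider numerator costs only wording: remove *confirmed* from the event definition and note in Appendix 3 that Table 3 does not govern this ORR, apart from the failed-confirmation rule in item 2. Choosing confirmed-only fits the stated reason for confirmation and uses a scan already scheduled, but it is more than wording. It changes the analysed endpoint in six cohorts and lowers the chance of an efficacy stop, for example from 50.6% to 29.3% in A and E if the counted ORR is 20% and the confirmed ORR 16%. The amendment should say so. A look may also wait about four weeks if pending responses are held until their repeat scan is read.

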response (confirmed or unconfirmed) or stable disease more than 24 weeks as defined as per RECIST v1.1 criteria.

- **For cohorts J (Urothelial cancer), K (HPV-associated cancer) and L (Triple negative breast cancer):** antitumor activity will be assessed in terms of disease control rate at 6-month (6-month DCR rate) based on RECIST 1.1 criteria after in-stream centralized radiological review. 6-month DCR rate is defined as the proportion of participants with confirmed complete response (CR), unconfirmed complete response (CRu), confirmed partial response (PR) or unconfirmed partial response (PRu) or stable disease (SD), as per adapted RECIST v1.1, observed within 24 weeks of treatment onset (while treated with the investigational product).

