#### **10.1.5. Phase II trial: Cohort A' (Colorectal @ 80 mg), with immune signature (based on low tumor-associated macrophages infiltrate level)**

- We rely on a single-arm phase 2 trial based on an optimal two-stage Simon's design [91].
- Treatment will be considered promising if 4-month PFR  $\geq 20\%$ .
- Hypotheses are the following:
  - 20% 4-month PFR (null hypothesis),
  - 40% acceptable 4-month PFR (alternative hypothesis),
  - 5% 1-sided type I error rate,
  - 80% power,
- A total of 43 eligible and assessable subjects will be necessary, with 13 assessable subjects recruited to the first stage.

- Stage 1: Following the inclusion of the first 13 assessable patients, if 3 or less patients are progression-free at 4 months (complete response, partial response or stable disease), the study will be terminated early. Otherwise, if 4 or more patients are progression-free at 4 months, the second group of subjects will be recruited.
- Stage 2: If at the end of recruitment, 13 patients or more are progression-free at 4 months (out of the 43 eligible and evaluable patients), treatment will be considered worthy of further testing in this disease (efficacy rate  $\geq 20\%$ ).
- Inclusions will not be suspended after the recruitment of the first 13 patients while data are being analysed for the first stage of inclusion.
- In order to account for not evaluable patients (+/- 10%), 47 patients will be recruited.

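### Cohort A': section 9 and the synopsis count stable disease towards 4-month PFR only beyond 24 weeks, while the Simon rule in 10.1.5 sets no duration

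*Protocol*

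**What the plan says.** Section 9.2.1 sets the endpoint for cohort A': "4-month PFR is defined as the proportion of patients with progression-free status at 4 months". It then defines progression-free status as complete or partial response, confirmed or not, "or stable disease more than 24 weeks as defined as per RECIST v1.1 criteria". The bullet just before it defines the 6-month rate for cohorts B, H, I and M to P with the same status definition.

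The synopsis repeats this for A': "response (confirmed or unconfirmed) or stable disease more than 24 weeks as defined as per RECIST v1.1 criteria". Section 9.2.2 gives one status definition, with the 24-week condition, and derives both the 6-month and the 4-month rates from it.

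Section 10.1.5 holds the design for A': null rate 20%, alternative 40%, one-sided type I error 5%, power 80%. "A total of 43 eligible and assessable subjects will be necessary, with 13 assessable subjects recruited to the first stage". The stage 1 rule reads: "if 3 or less patients are progression-free at 4 months (complete response, partial response or stable disease), the study will be terminated early". Final success needs 13 or more of 43. No duration is attached to stable disease. Section 10.3.2.2 likewise lists stable disease among the PFR categories without a duration.

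Imaging is every eight weeks within 7 days either way (section 5.5), and central review covers weeks 8, 16 and 24 (section 8.2.2.1).

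**The concern.** At 4 months no patient can yet have more than 24 weeks of stable disease, so the section 9 condition does not fit its own time point. It appears to have been carried over from the 6-month endpoint.

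Take a patient who is stable at week 16 and progresses by week 24. That patient is progression-free at 4 months and counts as a success in 10.1.5, but fails the definition in section 9. The null and alternative rates and both boundaries in 10.1.5 are stated for status at 4 months, so the endpoint definition and the design measure different things.

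The choice decides whether A' stops at stage 1 and whether it is called worthy of further testing. In an open-label single-arm cohort, that choice should not be left until outcomes are visible.

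**Working it through.** **Inputs from section 10.1.5.** p0 = 0.20, p1 = 0.40; n1 = 13, continue if 4 or more successes; N = 43, success if 13 or more.

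**The plan's own figure.** With X1 ~ Bin(13, p) and X2 ~ Bin(30, p):

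P(success) = sum over x = 4 to 13 of P(X1 = x) × P(X2 ≥ 13 − x)

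- p = 0.20: 0.0496 (type I error)
- p = 0.40: 0.8002 (power)
- Stage 1 stop, P(X1 ≤ 3): 0.747 at p = 0.20 and 0.169 at p = 0.40

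A search for the smallest expected sample size under p0, with type I error at most 0.05 and power at least 0.80, returns this same design. The design is therefore correct if stable disease at 4 months counts.

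**Effect of the 24-week condition, without a time model.** Suppose k of the 40 points are patients stable at 4 months but not beyond 24 weeks. The success probability becomes 0.40 − k:

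| k (points) | Success probability | Power |
|---|---|---|
| 0 | 0.40 | 80% |
| 2 | 0.38 | 74% |
| 5 | 0.35 | 63% |
| 10 | 0.30 | 41% |
| 15 | 0.25 | 19% |

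**With a time model.** The Protocol gives neither a hazard nor the split between response and stable disease, so these are assumptions: constant hazard, 40% progression-free at 4 months (w weeks), and responders at 4 months (share R) always counted. The fraction of stable patients still stable at 24 weeks is 0.40^((24 − w)/w):

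- w = 16 (the scheduled scan): 0.40^(8/16) = 0.632
- w = 17.4 (4 calendar months): 0.40^(6.6/17.4) = 0.706

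Success probability = R + (0.40 − R) × that fraction.

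| R | w = 16: success / power / stage 1 stop | w = 17.4: success / power / stage 1 stop |
|---|---|---|
| 0 | 0.253 / 20% / 57% | 0.283 / 32% / 48% |
| 0.10 | 0.290 / 36% / 45% | 0.312 / 46% / 38% |
| 0.20 | 0.326 / 53% / 34% | 0.341 / 60% / 30% |
| 0.30 | 0.363 / 69% / 25% | 0.371 / 71% / 23% |
| 0.36 | 0.385 / 76% / 20% | 0.388 / 77% / 19% |

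**Type I error.** The stricter definition can only remove successes. With no responders under the null, the success probability falls from 0.20 to 0.089 (w = 16) or 0.109 (w = 17.4), and type I error to 0.0003 or less.

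**The case against.** The strongest reply is that the operational rule is already right. Section 10.1.5 fixes the hypotheses, the boundaries and the power, and it counts stable disease at 4 months without a duration. Applied that way, the design delivers its 80% power. This stands, and it makes the point a contradiction between sections rather than a failed sample-size calculation.

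It does not settle which text governs. The primary objective (section 2.1.2) sends the reader to section 9 for the endpoint, and section 9 holds the 24-week wording. The bracketed list in 10.1.5 could also be read as shorthand: cohort H's rule in 10.1.3 uses the same list at 6 months, where section 9 also requires 24 weeks. At 6 months the two texts nearly coincide; at 4 months they do not.

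A second reply concerns size. The lowest power figures assume no responders. Section 1.1.1 cites a 36% response rate for low-dose regorafenib with nivolumab in colorectal cancer, and at that share power would be 76–77%. This also stands, as an illustration only: the figure comes from a different combination and is not a planning value for A'.

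A reader might infer that every patient stable at 4 months is scored a failure. That would follow only if status were fixed strictly at the 4-month scan. If later scans are used, patients stable beyond 24 weeks count, and only those who progress in between are lost. The documents do not impose the stricter reading.

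**Conclusion.** The primary endpoint of cohort A' is defined inconsistently: the synopsis, 9.2.1 and 9.2.2 on one side, 10.1.5 and 10.3.2.2 on the other. The 24-week condition does not fit a 4-month endpoint and should be removed.

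The consequence is conditional. Under 10.1.5, type I error is 4.96% and power 80.0%. Under the section 9 wording, power is below 80% in every scenario tried, from about 20% to about 77%, and the chance of stopping at stage 1 is 19% to 57% instead of 17%. That range rests on a constant hazard, on 40% progression-free at 4 months, and on a responder share that the Protocol does not state. The direction does not depend on those assumptions: the stricter wording can only lower the chance of success, so the risk is missed activity and not a false positive.

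A reader might conclude that the cohort is underpowered as designed. The documents do not support that, because the loss arises only if the section 9 wording overrides 10.1.5.

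**What to change.** For the 4-month rate only, delete the 24-week condition in the synopsis, 9.2.1 and 9.2.2. Define progression-free status for A' as alive with complete response, partial response or stable disease and no progression at the week-16 scan, within the scheduled window of 7 days either way. This matches 10.1.5. In 9.2.2, where one definition serves both rates, separate the 4-month status so that the 6-month definition is untouched.

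Keep the null and alternative rates, the 43 assessable patients and both boundaries. The cost is one sentence in an amendment, repeated in three places and carried into the SAP. No extra scans, data or patients are needed.

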#### **10.1.6. Phase II trial : Cohorts J (Urothelial cancer) and L (Triple negative breast cancer)**

- We rely on a single-arm phase 2 trial based on an exact single stage design (A'Hern).
- Treatment will be considered promising if 6-month DCR  $\geq 15\%$ .
- Hypotheses are the following:
  - 15% 6-month DCR (null hypothesis),
  - 35% 6-month DCR (alternative hypothesis),
  - 5% 1-sided type I error rate,
  - 80% power,
- A total of 28 eligible and assessable subjects will be necessary. If at the end of recruitment, 8 patients or more have disease control at 6 months (out of the 28 eligible and evaluable patients), treatment will be considered worthy of further testing in this disease (efficacy rate  $\geq 15\%$ ).
- In order to account for not evaluable patients (+/- 10%), 31 patients will be recruited.

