#### **10.1.7. Phase II trials: Cohort K (HPV-associated cancer)**

- We rely on a single-arm phase 2 trial based on an exact single stage design (A'Hern).
- Treatment will be considered promising if 6-month DCR  $\geq 10\%$ .
- Hypotheses are the following:
  - 10% 6-month DCR (null hypothesis),
  - 25% 6-month DCR (alternative hypothesis),
  - 5% 1-sided type I error rate,
  - 80% power,
- A total of 40 eligible and assessable subjects will be necessary. If at the end of recruitment, 8 patients or more have disease control at 6 months (out of the 40 eligible and evaluable patients), treatment will be considered worthy of further testing in this disease (efficacy rate  $\geq 10\%$ ).
- In order to account for not evaluable patients (+/- 10%), 44 patients will be recruited.

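### Cohorts J, K and L: the primary endpoint counts any disease control seen within 24 weeks, but the decision rule counts disease control at 6 months

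*Protocol*

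**What the plan says.** Section 9.2.1, and the Endpoints part of the Synopsis in the same terms, names the primary endpoint of cohorts J (urothelial), K (HPV-associated) and L (triple negative breast) a disease control rate at 6 months. It defines this as confirmed or unconfirmed complete or partial response, or stable disease, "observed within 24 weeks of treatment onset (while treated with the investigational product"). It sets no minimum duration of stable disease and does not require the patient to be free of progression at week 24.

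The 6-month progression-free rate (PFR) used for other cohorts, defined in the same section, does set a duration: "partial response (confirmed or unconfirmed) or stable disease more than 24 weeks as defined as per RECIST v1.1 criteria".

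The sample-size sections state the hypotheses as 6-month rates. For J and L they are "15% 6-month DCR (null hypothesis") against "35% 6-month DCR (alternative hypothesis"); for K the null is "10% 6-month DCR (null hypothesis") against an alternative of 25%. The treatment is judged worthy of further testing in J or L if "8 patients or more have disease control at 6 months (out of the 28 eligible and evaluable patients"), and in K if "8 patients or more have disease control at 6 months (out of the 40 eligible and evaluable patients").

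Section 5.5 schedules tumour assessment every eight weeks. Section 10.2.2 asks for at least one disease measurement eight weeks or more after the start of treatment. Section 10.3.2.6 plans no interim analysis for cohorts J to P.

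**The concern.** A rate of control ever seen within a window and a rate of control at a fixed time are different quantities, and the first is normally the larger. With eight-weekly scans, a patient who is stable at week 8 and progresses at week 16 meets the Section 9.2.1 definition but does not have disease control at 6 months. The same patient therefore has opposite primary outcomes depending on which section is followed.

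Each of these cohorts is single-arm and single-stage, so one count against a cut-off of 8 decides whether it is positive. If the count follows the looser definition while the null rate belongs to the stricter one, the 5% one-sided error rate that justifies the cut-off no longer applies.

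**Working it through.** **Step 1. Do the stated designs reproduce?** Inputs from Sections 10.1.6 and 10.1.7: J and L have n = 28, cut-off 8, p0 = 0.15, p1 = 0.35; K has n = 40, cut-off 8, p0 = 0.10, p1 = 0.25; one-sided error 5%, power 80%. The exact binomial tail is

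P(X ≥ 8 | n, q) = Σ (k = 8 to n) C(n, k) q^k (1 − q)^(n − k).

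- J and L: error P(X ≥ 8 | 28, 0.15) = 0.0486; power P(X ≥ 8 | 28, 0.35) = 0.818.
- K: error P(X ≥ 8 | 40, 0.10) = 0.0419; power P(X ≥ 8 | 40, 0.25) = 0.818.

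A search for the smallest n meeting both limits returns 28 and 40, each with cut-off 8. The sample-size arithmetic is correct.

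**Step 2. Which endpoint do the null rates belong to?** Section 10.1.9 (cohort N, 6-month PFR) uses 15% against 35%, n = 28 and cut-off 8, exactly as J and L do. Section 10.1.10 (cohort P, 6-month PFR) uses 10% against 25%, n = 40 and cut-off 8, exactly as K does. Together with the 6-month wording of the hypotheses, this suggests that p0 is a rate at 6 months. It is not proof, because Sections 10.1.6 and 10.1.7 cite no source for the rates.

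**Step 3. Error if p0 is a 6-month rate but the Section 9.2.1 definition is counted.** Let q be the proportion of patients on an inactive regimen who are ever stable or better within 24 weeks while on treatment. Apart from anyone who left treatment before a first scan, every patient controlled at week 24 also counts in q, so q is at least about p0. The documents give no value for q, so the values below are assumptions.

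| Assumed q | J, L: P(X ≥ 8 of 28) | K: P(X ≥ 8 of 40) |
|---|---|---|
| equal to p0 (15%; 10%) | 0.049 | 0.042 |
| 1.25 × p0 (18.75%; 12.5%) | 0.14 | 0.12 |
| 15% | 0.049 | 0.24 |
| 20% | 0.18 | 0.56 |
| 25% | 0.40 | 0.82 |
| 30% | 0.64 | 0.94 |

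**Step 4. A reference case under a further assumption.** If time to progression has a constant hazard, S(8) = S(24)^(8/24). For J and L, 0.15^(1/3) = 0.53; for K, 0.10^(1/3) = 0.46. The false-positive probabilities are then 0.998 and 0.9999. This is a consequence of the model, not a figure in the protocol.

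**Step 5. Does another passage settle the definition?** Section 10.2.2 governs who is assessable, not what counts as success. The primary-analysis text in Section 10.3.2.2 covers ORR and PFR and does not mention disease control. Appendix 3 refers to a minimum duration of stable disease when an unconfirmed response is downgraded, but gives no value. None of these resolves the conflict.

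**The case against.** The strongest reply is that the 6-month reading governs. The objective, the endpoint's name, the hypotheses and the decision rules all say 6 months, and the decision rules determine success. On that reading the error is 0.0486 and 0.0419 and nothing is lost. This is a fair account of what was probably intended, but it leaves standing an explicit definition in the endpoint section that says otherwise, and that is where an analyst would look to code the variable.

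A second reply is that 15% and 10% might be null rates for control at any time within 24 weeks. The error would then also be held. With no source cited this cannot be excluded, so the inflation above is conditional.

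A reader might infer three stronger things that the documents do not support.

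- *An inactive regimen is almost certain to pass.* The values above 0.99 need both a 6-month p0 and a constant hazard. The protocol states neither the source of p0 nor any hazard model, and smaller excesses of q over p0 give much smaller inflation.
- *A positive result would carry no information.* Section 9.2.2 makes the 6-month PFR a secondary endpoint in every phase II cohort. Section 10.3.2.2 computes it as patients alive without progression at 6 months over the eligible and assessable patients, with 95% limits. The fixed-time result would therefore be reported too, although it does not repair the primary rule.
- *The primary PFR has the same defect.* Section 10.3.2.2 does write "the progression-free rate (PFR: CR, CRu, PR, PRu, SD) will be reported" with no duration, but this is a shorthand list of categories. Section 9.2.1 already requires stable disease of more than 24 weeks for PFR.

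**Conclusion.** The contradiction is established from the text alone: Section 9.2.1 and the Synopsis define one endpoint for J, K and L, and Sections 10.1.6 and 10.1.7 test another. It needs correcting before the primary analysis because it can change which patients count as successes.

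The loss of error control is conditional. It requires that p0 is a 6-month rate, which the wording and the match with cohorts N and P make likely, and that patients are counted by the Section 9.2.1 definition. Under those two conditions, even a null rate only 1.25 times p0 raises the one-sided error from the planned 5% to 0.14 (J, L) or 0.12 (K), and a rate of twice p0 raises it to 0.64 or 0.56. How far q exceeds p0 is not known from the documents. The sample sizes and cut-offs are correct for the rates as stated.

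**What to change.** - In Section 9.2.1 and the Synopsis, define 6-month disease control for J, K and L as CR, CRu, PR, PRu or SD at the week-24 assessment, with no progression or death before it.
- State how a patient who has stopped study treatment but is progression-free at week 24 is counted. The present definition restricts observation to time on treatment, and Section 5.2 moves patients who stop without progression to 12-weekly follow-up.
- Add the disease control rate, with this numerator, to the primary analysis in Section 10.3.2.2.
- Have the sponsor confirm, with a source, that 15%/35% and 10%/25% are rates at 6 months. If so, p0, p1, n and the cut-offs stay as they are, with error 0.0486 and 0.0419 and power 0.818. If control at any time within 24 weeks was intended, p0, p1, n and the cut-off must be re-derived for that endpoint and the name and decision rules changed to match.
- As a wording note only, let the PFR list in Section 10.3.2.2 refer back to stable disease of more than 24 weeks.

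If the 6-month reading is confirmed, the cost is amendment and SAP wording. Section 8.2.2.1 already schedules central review at week 24, so no scan is added for patients on treatment. Observed rates will be lower than under the looser definition.
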